## Abstract

**Background:**

Alcohol-related harm is currently estimated to cost the National Health Service (NHS) in England £3.5 bn a year. Of the estimated 1.6 million people with some degree of alcohol dependence, some 600,000 are believed to be moderately or severely dependent and may benefit from intensive treatment. Outcomes from medically assisted withdrawal, also referred to as detoxification, are often poor, with poor engagement in relapse prevention interventions and subsequent high relapse rates. Detoxification is costly both financially and to the individual. It has been found that people who experience multiple detoxifications show more emotional and cognitive impairments. These changes may confer upon them the inability to resolve conflict and increased sensitivity to stress thus contributing to increased vulnerability risk of relapse. The study aims to test the feasibility of using a group intervention aiming to prepare participants for long-term abstinence before, rather than after, they have medically assisted detoxification. The current study will establish key parameters that influence trial design such as recruitment, compliance with the intervention, retention, and sensitivity of alternative outcome measures, in preparation for a future randomised controlled trial (RCT). This paper presents the protocol of the feasibility study.

**Methods:**

The study corresponds to phase 2 of the Medical Research Council (MRC) complex interventions guidelines which cover the development and feasibility testing of an intervention. The work is in three stages. The development, adaptation and implementation of the Structured Preparation before Alcohol Detoxification (SPADe) intervention (stage 1), a randomised feasibility study with economic evaluation (stage 2) and a qualitative study (stage 3). Fifty participants will be recruited from two community alcohol treatment services in England. Participants will be randomised in two arms: the treatment as usual arm (TAU), which includes planned medically assisted detoxification and aftercare and the intervention arm in which participants will receive structured group preparation before detoxification in addition to TAU. The main outcomes are duration of continuous abstinence with no incidents of lapse or relapse, percentage of days abstinent and time to relapse.

**Discussion:**

The socioeconomic harms associated with alcohol have been well-documented, yet existing treatment options have not been able to reduce high relapse rates. This study will build on existing naturalistic studies underpinned by psychological interventions offered early and before detoxification from alcohol, which aim to reverse automatised habitual behaviours and thus may help us to understand how better to support people to remain abstinent and improve post detoxification outcomes.

**Trial registration:**

ISRCTN, 14621127; Registered on 22 Feb 2017

## Background

Tackling the impact of harmful and dependent drinking is a key global public health priority. Harmful drinking refers to consuming alcohol at amount and patterns that would affect the person’s physical and mental health and lead to personal and social harm. The harm is linked to both chronic as well as episodic heavy use (intoxication). For example, global estimates suggest that one in five adults report at least one occasion of heavy episodic drinking in the past month [1]. Alcohol harmful use is linked directly to a range of health disorders, including high blood pressure, heart disease, stroke, liver disease, some cancers and depression [2]. Furthermore, more than 21,000 people died from alcohol-related causes in England in 2012 [2]. As far as financial cost is concerned, estimates suggest that alcohol-related harm (from harmful and dependent use) costs the National Health Service (NHS) in England £3.5 bn a year [2].

Despite the fact that the prevalence of dependent drinking is far less than that of harmful drinking, of an estimated 1.6 million people with some degree of alcohol dependence, some 600,000 are believed to be moderately or severely dependent and may benefit from intensive treatment [3]. Individuals who are ‘moderately’ or ‘severely’ dependent represent the severe end of the spectrum of alcohol use disorders and consume alcohol at levels that are likely to have a severe impact on their own health and mortality, the health and behaviours of others (family members) and to have economic and social implications [4]. Alcohol dependence impacts significantly on the NHS, as individuals affected are at increased risk of accidents, and more likely to attend an accident and emergency department (A&E) and have emergency admissions [2, 5]. In the longer term, alcohol-dependent individuals are more likely to suffer from chronic conditions requiring expensive treatment, such as liver and heart disease [2].

Current treatment guidelines suggest that treatment for moderate to severe alcohol dependence needs to be planned, with up to four motivational sessions focusing on treatment engagement and development of aftercare support, followed by medically assisted withdrawal (also referred to as detoxification) and aftercare support [4]. Benzodiazepines are normally prescribed during detoxification to reduce the overt symptoms of alcohol withdrawal (sweats, tremor) as well as potentially life-threatening complications (e.g. convulsions, delirium tremens) [4]. However, these drugs do not prevent alcohol craving, relapse back into alcohol drinking and other long-term effects on mental functioning [4, 6]. Outcomes from detoxification are often poor with low proportions engaging in aftercare [7] and high relapse rates [4]. Repeat detoxification is costly. Additionally, there is some evidence suggesting that people with alcohol dependence who experience multiple detoxifications show increased impairment in mental functioning [8, 9]. It is important to clarify that these changes are shown to be associated, not caused by the detoxification process. Nevertheless, they may confer inability in conflict resolution and increased sensitivity to stress, both of which may contribute to relapse and might compromise the effectiveness of aftercare support [8–11]. There is also evidence to suggest that multiple detoxifications can exacerbate craving, adversely impacting on subsequent attempts at achieving abstinence [12].

In the light of the abovementioned evidence indicating the potential risk of an accumulation of adverse effects following repeated detoxifications, and until definitive evidence is generated to confirm or refute a causal relationship, it is prudent to maximise treatment effectiveness and to reduce the risk of exposing people to repeated detoxifications and the potential adverse effects associated with the detoxification process itself. Although the existing evidence is only indicative, it is possible that the long-term course, and economic and social impact of alcohol dependence, is not only due to the natural process of the phenomenon, but is also associated with the existing treatment approach that emphasises the importance of the provision of detoxification per se, without any emphasis on long-term sustainable outcomes. There is currently no guidance specifically on preparation for the detoxification process, apart from general guidance on care coordination and case management [4]. Absence of specific guidance reflects the lack of developed interventions in this area. Evidence is required on whether structured preparation before detoxification rather than detoxification alone improves treatment outcomes and therefore whether the whole treatment paradigm should shift. Before embarking on a full trial of the effectiveness of such structured preparation, there is a need to undertake a feasibility study to establish key parameters that influence trial design such as recruitment, adherence to the intervention, retention and sensitivity of alternative outcome measures.

A literature search of PubMed Central using alcohol relapse prevention, treatment-related MeSH terms undertaken in June 2014 found (1) that group interventions with diverse theoretical bases are considered to be more cost-effective than one-to-one interventions [13] and (2) cognitive behaviour therapy (CBT) relapse prevention interventions are well-supported by evidence [14].

In the UK, an innovative group intervention for preparation before alcohol detoxification, based on CBT relapse prevention interventions, developed by members of the research team, reduced detox dropouts [15] and improved outcomes at 1, 3 [5] and 6 months [16]. However, these findings were from small naturalistic studies. Qualitative evidence found that ‘regaining control’ was the main learning point across all group sessions of the programme [17].

This proposed feasibility study builds on the above preliminary evidence and aims to refine the preparatory intervention and assess the feasibility of conducting a large-scale evaluation (Structured Preparation before Alcohol Detoxification (SPADe)) for people with moderate to severe alcohol dependence, as an adjunct to usual care, consisting of planned detoxification and aftercare.

The intervention under investigation in this study is based on Plans, Responses, Impulses, Motives, Evaluations (PRIME) theory of motivation [18] and learning theories [19] that underlie the use of psychological interventions aiming to reverse the development of automatised behaviour and associated loss of control, such as CBT relapse prevention interventions. It combines the long-established (in alcohol treatment) ethos of group intervention and follows the biological principle of homeostasis, which is disturbed with prolonged alcohol use [20], in order to help individuals to regain control over drinking as the first step towards lifelong sustainable abstinence.

## Aims and objectives

The key research question is can we design a large-scale, randomised controlled trial (RCT) that will answer whether SPADe as an adjunct to usual care is more effective than usual care alone in helping adults to maintain longer periods of alcohol abstinence? The feasibility trial will compare the use of SPADe as an adjunct to treatment as usual with treatment as usual in the participating sites.

Furthermore, reduction in subjective measures of alcohol dependence and craving as well as improvement in objective measures of mental functioning will be explored. Finally, we will conduct qualitative interviews with service users, their carers and service providers, to assess the acceptability of the treatment and to explore their experience of the treatment including any barriers and/or facilitators to taking part in the study. Findings from these interviews will enable us to refine the SPADe intervention and the design of the future definitive RCT.

## Methods/design

The study corresponds to Phase 2 of the Medical Research Council (MRC) complex interventions guidelines, which guides the development of an intervention [21]. Therefore, the study has three stages:

### Stage 1—adaptation and implementation of the intervention

We will adapt the existing pre-alcohol detox group protocol [6, 16, 17] by incorporating feedback from service users and group facilitators gathered at two patient and public involvement (PPI) meetings to produce a manual for the intervention. Group facilitators will be recruited from existing staff and trained in the intervention via the use of the manual. When training is complete, we will implement the SPADe groups across our two study sites.

A 1-day training event will take place in each participating site and one central event for those not able to attend locally. At least six members of staff will be trained (to allow cross-cover for sickness and leave). Facilitators will have face-to-face or Skype supervision at least monthly or more frequently if required weekly by the chief investigator.

Importantly during this phase, treatment as usual procedures will also be standardised across the sites. To reduce the risk of contamination between the intervention and the control arms of the study, the trained intervention group facilitators will offer only the intervention and they will not undertake individual work with any service user for the period of the study. They will also provide the one-to-one version of the intervention to non-English speaking service users (via an interpreter if required). The rest of the staff will provide the treatment as usual.

### Stage 2—feasibility study

#### Design

This is a single-blind (outcome assessor blind to allocation), parallel, two-arm, feasibility RCT comparing the clinical effectiveness of SPADe as an adjunct to treatment as usual (TAU), against TAU. Participants will be assessed at baseline, 3, 6 and 12 months following randomisation. Additionally, qualitative interviews will be carried out at 3 and 9 months (see stage 3 below).

#### Setting

Participants will be recruited from specialist alcohol community services offering recovery-orientated treatment for people with alcohol use disorders (AUD). Recruitment will take place in two sites, both offering the intervention and the treatment as usual, in order to explore challenges associated with implementation of the intervention across a range of services.

#### Participants

We will recruit 50 alcohol-dependent participants, aged 18 or over who have a desire to stop drinking. As both recruiting services operate within a multi-lingual, multi-faith and multi-cultural environment, we will provide study information in the two most prevalent languages spoken by non-English speakers in our locations, in addition to the material in English. Should we recruit any non-English speaking participants to the intervention arm, the sessions will be provided in one-to one format by the intervention group facilitator, with the support of an interpreter if required. Participant flow to the study is shown in Fig. 1. We will aim to recruit at least one of the above participants in the qualitative study to explore their experience.

**Fig. 1 Fig1:**
[figure not shown]
Recruitment and follow-up flow diagram

#### Recruitment

When entering the service, eligible service users will be advised about the study by the clinician undertaking the initial assessment, following the completion of the assessment. If interested, the service user will be given the participant information sheet and a member of the research team will contact them a few days later to ascertain if they would like to be recruited into the study. An arrangement will be made to meet in the clinic to take informed consent and collect baseline information. Participants will receive a £10 shopping voucher (not valid for alcohol purchase) per completion of each research assessment throughout the trial (four in total, with additional two vouchers if they take part in the qualitative study, see below) (see Fig. 1).

#### Inclusion criteria

Inclusion criteria are as follows:Presentation to either of the two alcohol services seeking abstinence from alcohol.Alcohol dependence (moderate to severe), scoring 16 and above on Severity of Alcohol Dependence Questionnaire (SADQ) (see the ‘Outcome measures’ section below). This level of dependence indicates that it would be clinically appropriate to receive a medically assisted detoxification [4].Stated intention to stay in the area within the time period of the intervention.Willingness to be part of a group intervention if randomised to receive it.

#### Exclusion criteria

Exclusion criteria are as follows:Age less than 18 (as not usually treated by specialist alcohol services).Pregnancy: pregnant women need urgent intervention to withdraw from alcohol, due to the effect of alcohol on the foetus.Known terminal illness with life expectancy of less than 6 months.Severe medical condition that requires urgent medical admission, which would lead to an unplanned medically assisted withdrawal.Severe cognitive impairment that compromises capacity and/or ability to participate in a group intervention.Acute stage of severe and enduring mental illness (schizophrenia, bipolar affective disorder, recurrent depressive disorder—current episode severe), when acute symptomatology compromises service user’s ability to participate in a group intervention.

#### Trial arms

##### Treatment as usual

Usual detoxification/control comprises planning for detoxification, detoxification delivery and aftercare. Standardised procedures across sites will be confirmed in phase 1. Service users enter detoxification at the first available opportunity (likely to be within 4 weeks from presentation). Whilst waiting for detoxification, they will meet their key worker (one-to-one) on 3–4 occasions to maintain motivation and plan aftercare.

Detoxification is medically assisted in the community as an outpatient, or inpatient, as clinically indicated. The choice depends on health risk factors and availability of social support during detoxification. The type of detoxification has been shown by NICE not to affect treatment outcomes [4]. Aftercare (following detoxification) includes peer support groups such as Self-Management and Recovery Training (SMART) Recovery or Alcoholics Anonymous (AA), a small number of individual key worker sessions, pharmacological interventions as appropriate or more comprehensive aftercare group programme. Participants in both intervention and control groups will receive all the above elements of usual care available in the recruiting service. Each participant’s care pathway will be recorded in detail and analysed for variability within and between sites as part of the economic evaluation (see below), to ensure these are equivalent across trial arms.

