##### Intervention

The intervention provides structured group preparation (additional to usual care) with the aim of helping participants regain control over their drinking, prior to detoxification. Part of this control is lifestyle modification, which is necessary for maintaining abstinence post detoxification. Regaining control is linked with developing new coping skills and enhanced self-efficacy.

The six sessions are numbered and offered weekly in a given order. Stabilisation of the amount and pattern of drinking is a common theme across all the sessions. To that effect, each session can act as an entry point (i.e. an open rolling programme group), despite the special theme covered in depth during the second part. Each session has two facilitators, lasts for 1 h and is divided into three parts:In the first part (15 min), group rules are established (as advised in PPI meetings), new members are introduced, aims of the intervention, in-between sessions practice allocated in previous session reviewed as are individual targets set for the previous week are reviewed.The second part (30 min, main part) explores the following themes depending on the session number: 1—understanding habit, addiction and alcohol dependence; 2—stabilise and control your drinking; 3—lifestyle changes for you and the people around you; 4—reduction of your drinking; 5—achieving abstinence; and 6—relapse prevention strategies.In the third part (15 min), the group summarises the main learning points and agrees in-between sessions practice and targets to be achieved before the next session. A group work folder will be provided enabling notes and worksheets to be kept together, as also suggested by PPI meetings.

The number of participants per group at any point is between two and eight, as this is considered appropriate for theory-based treatment groups, to reach a balance between education, treatment, group interactions and facilitator’s attention to each participant [13]. This maximum is unlikely to be reached in the feasibility trial. If only one participant is present, the session will be offered by one of the facilitators as an individual session. The duration of 1 h as suggested in PPI, will reduce risk of withdrawal symptoms and help participants to maintain concentration.

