#### Outcome measures

Feasibility outcomes will be (1) Recruitment and retention rates: we will monitor (monthly) the number of alcohol-dependent clients accessing services during the recruitment period of the study, how many meet the eligibility criteria and how many were invited and accepted into the study and retained in each group for the full 12 months. (2) Compliance with treatment: number of SPADe sessions attended (for the intervention arm) using the facilitator’s record of attendance. (3) Data collection and completeness: attendance for assessments and completeness of instruments; loss to follow-up and missing data for all outcomes will be analysed.

A variety of possible outcomes will be used, assessed at different time points (3, 6 and 12 months following randomisation), so the primary outcome for the main trial can be identified and sample size calculations conducted, including duration of continuous abstinence with no incidents of lapse or relapse; percentage of days of abstinence (PDA) (both self-report using Timeline Followback method (TLFB)) [22]; and time to relapse (from stopping alcohol to first day of alcohol use, also as defined by self-report).

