Secondary outcomes will be measured using validated instruments wherever possible at the same time points as above:Severity of Alcohol Dependence Questionnaire (SADQ), a 20-item self-completion questionnaire, scores range 0 to 60 (16 to 29 indicates moderate severity, above 30 severe dependence) [23].Alcohol Urge Questionnaire (AUQ), an eight-item self-completion questionnaire containing three domains of drinking urges: desire for a drink, expectation of positive effect from drinking and inability to avoid drinking [24].Incentive conflict task (ICT). We have introduced the ICT as incentive conflict task (ICT), a newly developed task which models contributors to relapse (inherent conflict in abstaining drinkers between the intention to abstain from drinking, and the desire to drink) [9]. The ICT requires experimental subjects to abstain from responding during the presentation of a novel compound stimulus made up of two visual cues that she/he has previously learned to signal reward availability when presented separately. Thus, the task requires the subject to respond for the monetary reward, but to withhold responding under conditions in which an increased size of reward (both positive cues together) might be reasonably anticipated. In other words, ICT engages both bottom-up triggers of reward-seeking and the top-down processes that normally modulate and veto responses to such triggers. We have suggested that the task thus creates a conflict between abstaining and responding for reward similar to that experienced by the patients before relapse and that the impaired ability of multiple-detoxified patients to perform the task accurately reflects the consequences of detoxification on top-down control of their behaviour. Alcohol-dependent patients, as they experience successive detoxifications and their alcohol dependence increases, become increasingly impaired in performing the ICT [25].Euro-QoL (EQ-5D-5 L); English version [26], which is a short questionnaire assessing general healthcare used in economic evaluations for the calculation of quality-adjusted life years.Self-reported participation in aftercare activities, using a specifically developed log, measuring type and frequency of activity attended, during the period prior to the follow-up interview.

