#### Economic evaluation and analysis

The economic evaluation that will run alongside the future trial will assess the cost-effectiveness of the SPADe intervention, compared to usual care, from the NHS and wider public service perspective. Economic evaluation is required in the feasibility study to inform decisions about how costs and outcomes would be measured in any future definitive trial.

The feasibility study will seek to gain an understanding of the main resource items for which comprehensive data collection would be required in the main trial. The resources involved in delivering the intervention will be collected from providers and will cover human resources, facilities, materials and overheads, so that full economic costs and average costs per participant can be calculated. Usual care (received by both arms) may vary. Hence, data on care provided will be collected on an individual client basis from clinic records so that variability can be explored both within and between groups.

Alcohol dependence can give rise to significant use of health, social and criminal justice services. The cost of implementing SPADe may be offset if it results in increased numbers of successful detoxifications and consequent reductions in alcohol-related utilisation of these services. To capture this possible effect, data on service utilisation will be gathered retrospectively from participants at 3-, 6- and 12-month assessments by self-report. The Client Service Receipt Inventory, customised in collaboration with service users, will be used for this purpose. Included items will cover GP, mental health services, specialist alcohol services, A&E attendance, inpatient stays and contact with social and criminal justice services. Items of service use will be converted to costs (British pounds, 2017) using nationally validated sources [28, 29] and national reference costs for secondary care (https://www.gov.uk/government/publications/nhs-reference-costs-2012-to-2013). Service use data will be analysed descriptively to assess validity.

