## Discussion

The SPADe trial builds on previous work completed by the authors, which has shown that a structured preparation approach prior to alcohol detoxification can improve overall capacity of the treatment pathway by increasing patients’ engagement and by reducing dropout rates from detoxification [6, 15]. Two open studies indicated that the intervention improves outcomes (continuous abstinence) at 3 [15] and 6 months [16]. A qualitative study with service users who have completed the intervention [17] and a process study [33] have indicated that the theory-based intervention works as expected and predicted by the underpinning theory.

This feasibility trial will help us to answer questions of acceptability of the intervention by wider group of service users, carers and service providers. It will provide evidence on implementation issues such as the training, supervision and overall support required to implement the intervention. In more detail will enable us to do the following:Measure the number of eligible participants and those not, willingness of clinicians to recruit participants, recruitment rate, loss to follow-up, adherence to the intervention and standard deviation of the primary outcome measures. This will ultimately inform the sample size calculation for a multi-centre clinical trial.Determine the acceptability of randomisation to service users, through its effect on recruitment, dropout rates and via qualitative interviews.Determine, through response rates to questionnaires, the appropriateness and the acceptability of the outcome measures to service users, in order to explore the suitability of our chosen secondary outcome measures, that is, percentage of days of abstinent, service use and health-related quality of life.Estimate the time needed to collect and analyse baseline and outcome dataExplore the utility of the health-related quality of life instrument (EQ-5D-5 L) (see the ‘Outcome measures’ section) in allowing the estimation of quality-adjusted life years in the sample.

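### Detoxification start, completion, dropout and repetition are not outcomes, although improving them is part of the rationale, and the care pathway is treated as something to be made equal between arms

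*Protocol article*

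**What the plan says.** **Rationale.** The Background argues that it is prudent "to reduce the risk of exposing people to repeated detoxifications and the potential adverse effects associated with the detoxification process itself". The Discussion credits the authors' earlier work with "increasing patients’ engagement and by reducing dropout rates from detoxification". The section Economic evaluation and analysis expects the cost of SPADe to be offset if it brings "increased numbers of successful detoxifications and consequent reductions in alcohol-related utilisation of these services".

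**Timing.** Under Treatment as usual: "Service users enter detoxification at the first available opportunity (likely to be within 4 weeks from presentation". Under Intervention: "The six sessions are numbered and offered weekly in a given order", and these sessions come before detoxification.

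**Outcomes.** Outcome measures lists three feasibility outcomes (recruitment and retention, SPADe sessions attended, data completeness), three candidate primary outcomes (continuous abstinence, percentage of days abstinent, time to relapse) and five secondary outcomes (SADQ, AUQ, incentive conflict task, EQ-5D-5L, aftercare log). Time to relapse is given there as "time to relapse (from stopping alcohol to first day of alcohol use". The Statistical analysis section instead measures it from the end of the intervention.

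**Pathway data.** Under Treatment as usual, a detailed record is kept of the care pathway of every participant, and these records are to be "analysed for variability within and between sites as part of the economic evaluation (see below), to ensure these are equivalent across trial arms". The economic section adds individual clinic-record data on usual care, explored within and between groups, and self-reported service use at 3, 6 and 12 months.

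**The concern.** Detoxification is the treatment step that both arms share, and SPADe adds up to six weekly sessions ahead of it. Whether participants reach detoxification, finish it, abandon it or need another is decided after randomisation and belongs to what SPADe is expected to improve. The article makes none of this an outcome, and it describes the data that would show it as a check that the arms are alike. A difference between arms could then be read as a failure of standardisation when it is an effect of the intervention, in either direction.

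The second consequence concerns time to relapse. A clock that starts when drinking stops exists only for those who stop. If the arms differ in how many get that far, the comparison is between two selected groups, and nothing stated alongside it would tell the reader so. The study is meant to choose the primary outcome for a definitive trial, so this affects how well time to relapse can be judged as a candidate.

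**Working it through.** There is no stated figure to reproduce: the article gives no sample size calculation for its 50 participants and no detoxification rates. The check is therefore mainly of the text.

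**1. Do the outcomes count detoxification events?** Each list was searched for start, completion, abandonment or repetition of detoxification.

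| List (Protocol article) | Items | Items counting a detoxification event |
|---|---|---|
| Feasibility outcomes | 3 | 0 |
| Candidate primary outcomes | 3 | 0 |
| Secondary outcomes | 5 | 0 |
| Instruments in Table 1 | 6 | 0 |

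Compliance means attendance at SPADe sessions only. Aftercare participation is an outcome, but the detoxification that precedes it is not. The number of earlier detoxifications appears under Randomisation and masking, as a baseline stratification factor.

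**2. Are the events captured anywhere?** Yes, in three sources: the care-pathway record, the clinic records and the service-use inventory (which includes specialist alcohol services and inpatient stays). All three serve the economic evaluation. The article does not define a successful detoxification and states no summary of detoxification events by arm.

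**3. Can the listed outcomes stand in for them?** Continuous abstinence and percentage of days abstinent cover everyone randomised. Neither separates a participant who never reached detoxification from one who completed it and relapsed.

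**4. Who is in the time-to-relapse comparison?**
- Origin under Outcome measures: the day drinking stops. A participant who never stops has no start date and no value.
- Origin under Statistical analysis: the end of the intervention. The TAU arm has no SPADe sessions, so no such date is evident for it. In the SPADe arm the sessions precede detoxification, so a participant may still be drinking on that date.

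The two origins define different populations and different durations.

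**5. How precise would a detoxification outcome be?** Assume 25 per arm (50 participants; the allocation ratio is not stated) and a common rate p in both arms. The 95% half-width for a difference in proportions is 1.96 × √(2p(1−p)/25).

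| Assumed p | Calculation | Half-width |
|---|---|---|
| 0.5 | 1.96 × √(0.50/25) | ±28 points |
| 0.7 | 1.96 × √(0.42/25) | ±25 points |
| 0.8 | 1.96 × √(0.32/25) | ±22 points |
| 0.9 | 1.96 × √(0.18/25) | ±17 points |

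These outcomes could only be descriptive, which agrees with the descriptive main analysis that the Statistical analysis section announces.

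**The case against.** The strongest reply has four parts.

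*The data are there.* Pathways are recorded per participant, and clinic-record data are to be explored between groups as well as within them. This stands. A reader might infer that loss before detoxification, or extra detoxifications, would go unseen; the documents do not support that. What is lacking is outcome status, a definition and a stated summary by arm.

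*The main abstinence results are protected.* The analysis is by intention to treat, continuous abstinence runs from randomisation, and percentage of days abstinent is analysed by regression. This also stands. Only time to relapse is exposed to the subset problem, and its extent depends on which origin is adopted.

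*The sentence has a milder meaning.* It follows a statement that both arms receive all elements of usual care available in the service, so it may intend only a check that usual care is offered alike. That is a fair reading of the intent. But the words cover the whole recorded pathway, and detoxification delivery is part of usual care as the article defines it. Analysis after the fact can describe equivalence; it cannot ensure it.

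*This is a condensed article.* The candidate outcomes are introduced as a list that need not be complete, and descriptive tables may be left to a fuller document. That weakens any complaint about omission alone. It does not answer the equivalence wording or the conflicting origins, which are in the text.

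Two further inferences fail. The incentive conflict task is said to capture how impaired performance "reflects the consequences of detoxification on top-down control of their behaviour", and one might conclude that a difference between arms on it could not be interpreted without a later detoxification count. It remains a randomised comparison, and randomisation is stratified by previous detoxifications. Nor is repeat detoxification the only harm in view: relapse and poor aftercare engagement are also part of the rationale, and both are measured.

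**Conclusion.** The point holds in a limited form. Detoxification start, completion, dropout and repetition are part of the stated rationale but appear in none of the outcome lists. They are held as resource-use data with no stated summary by arm, and one sentence treats a possible effect of SPADe as something to be equalised. Time to relapse, under its Outcome measures definition, compares subsets formed after randomisation unless it is shown with the proportion who reached detoxification. Its two stated origins contradict each other.

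No bias can be quantified, because the documents contain no detoxification rates. The precision figures rest on the assumed 25 per arm and assumed rates. The gap limits what the trial can say about loss along the pathway and about time to relapse as a future primary outcome. It does not undermine the intention-to-treat results for continuous abstinence or percentage of days abstinent.

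**What to change.** 1. Under Treatment as usual, replace the aim of ensuring equivalence with a descriptive comparison of the care pathway by arm.
2. Add as descriptive outcomes, by arm, over all randomised participants and 12 months: detoxification started, and time to it from randomisation; detoxification completed; dropout from detoxification; unplanned medically assisted withdrawal; and number of further detoxifications. Define completion beforehand.
3. Take these from the pathway and clinic records already collected. Clinic records may miss detoxifications delivered elsewhere; the self-reported service-use inventory may fill part of that gap.
4. Present time to relapse beside the proportion of all randomised participants who reached detoxification, and reconcile its origin between Outcome measures and Statistical analysis.
5. Do not tabulate the incentive conflict task by detoxifications since randomisation. That would condition on a variable SPADe may affect, in very small cells.

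The cost is some rewording and a few more descriptive tables, imprecise at about 25 per arm. Sample size, visits and procedures do not change.
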